i. To assess the frequency and intensity of the health state fluctuation, caregivers document if patients' today's health is much (+2) or somewhat better today (+1), about the same (±0) today, or somewhat (−1) or much (−2) worse today compared to the day before. Also, a repeated administration of the EQ-5D-5L will also assess the health state fluctuation as a self- and proxy-rating at baseline (before starting the diary), seven days after starting the diary, and on the last day of the diary (day 14). The change in the EQ-5D-5L utilities, EQ-5D-5L level scores and level sum scores (LLS), and EQ-VAS scores from day 1 to day 7 and day 7 to day 14 can be used to assess the variability and reliability of each measure.ii. To assign health state fluctuations to specific health dimensions, we will use the health dimension of the diary and the assessment of EQ-5D-5L dimensions at baseline, seven, and 14 days. The caregiver will be instructed to document in the diary which dimensions could be assigned to the fluctuation of today's health state compared to the day before. We will use dimensions of the EQ-5D-5L and two other patient-reported outcomes measures (PROMs), the EQ Health and Wellbeing instrument (EQ-HWB) (22) and the dementia-specific Quality of Life–Alzheimer's Disease (QoL-AD) (23). The EQ-HWB has been designed as a standardized measure of aspects of health and well-being and has 25 items (24). In comparison, the QoL-AD is a widely used measure of the quality of life in dementia diseases that contains 13 items evaluating the domains of interpersonal relationships, financial difficulties, physical condition, memory, mood and overall health. Furthermore, caregivers could specify any other affected dimensions not listed in the diary. All dimensions are shown in Figure 2.iii. Caregivers will also be asked to document any health events that could have caused the health state fluctuations.iv. To evaluate the consideration of past health state fluctuations in the assessment of today's health, the EQ-5D-5L will be administered on day 14. Subsequently, the caregivers will be interviewed and asked whether or not recurrent health state fluctuations (if applicable) were considered in the assessment of health today using the EQ-5D-5L administered minutes before starting the interview. Furthermore, the caregiver will be asked to state what recall period would be more appropriate to assess HRQoL in people living with dementia more accurately.

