### Statistical analyses

#### Quantitative data preparation and analyses

Patient and caregiver characteristics will be demonstrated descriptively. Descriptive statistics will also describe health state fluctuations' occurrence, frequency, and intensity. The occurrence will be operationalized dichotomously: no fluctuations reported vs. at least one fluctuation reported. The frequency will be quantified as the number of fluctuations within 14 days. The intensity will be operationalized as follows: much worse or better = ±2; somewhat worse or better = ±1; about the same = ±0) of the reported health events. We will demonstrate the intensity of the health state fluctuations as a mean change per day with standard deviation.

Furthermore, we will use exploratory data analysis of the EQ-5D-5L data by reporting the number and percentage of patients reporting each level on each dimension of the EQ-5D-5L using simple descriptive statistics (26). The EQ-5D-5L profile and EQ-VAS scores will also be demonstrated using descriptive statistics. Also, change in EQ-5D-5L index, EQ-VAS and LLS will be demonstrated descriptively [mean value of change, Intra Class Correlation (ICC)] over the fluctuation intensity. Furthermore, cluster analyses will be used to identify frequent health events or a combination of events.

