To assess the association between occurrence, frequency and intensity of the reported health fluctuation and (i) the differences between the baseline, 7-day and 14-days follow-up EQ-5D-5L profile, health utility and EQ-VAS as well as the (ii) reporting of consideration of these health state fluctuations in the assessment of health today in the EQ-5D-5L, we will use appropriate statistics such as cross tables with ANOVA, *t*-tests and multiple logistic regression models. According to the latter one, multivariate regression models will include the adherence to the recall period (dichotomous: yes, no) as a dependent variable and the fluctuation intensity (low, moderate, high) and further socio-demographic and clinical variables of the patient as an independent variable. We hypothesize that frequent and more intensive health fluctuations reported in the diaries will cause higher variability of the EQ-5D-5L index between baseline and seven or 14 days later and will have higher odds for consideration of these fluctuations in the assessment of HRQoL today (non-adherence to the recall period of today). Additionally, we will use descriptive statistics to identify specific health events most likely affecting the incorporation into the health assessment today. Statistical analysis will be carried out in SAS (version 9.4 M7).

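### Fluctuation intensity is summarised as a mean of signed daily changes with no magnitude step, so read literally it measures net direction and not fluctuation

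*Protocol article*

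**What the plan says.** All references are to the Protocol article.

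- **Diary coding** (Outcome measures to assess health fluctuations, item i). The scale carries a sign: "caregivers document if patients' today's health is much (+2) or somewhat better today (+1), about the same (±0) today". Deterioration takes the mirror-image scores of −1 and −2, and every score is relative to the previous day.
- **Levels restated** (Quantitative data preparation and analyses). Intensity is set out as "much worse or better = ±2; somewhat worse or better = ±1; about the same = ±0".
- **Summary of intensity** (same section). "We will demonstrate the intensity of the health state fluctuations as a mean change per day with standard deviation". The text does not say whether the mean and SD are taken within each patient or across patients.
- **The two companion measures** (same section). Occurrence is "no fluctuations reported vs. at least one fluctuation reported". For frequency: "The frequency will be quantified as the number of fluctuations within 14 days".
- **Use of intensity.** It belongs to the first primary outcome. Changes in the EQ-5D-5L index, EQ-VAS and level sum score are to be presented over it. The regression on adherence to the recall period has as its named fluctuation predictor "the fluctuation intensity (low, moderate, high" in the article's list of classes. How the classes are formed is not stated.
- **Expectation.** More frequent and more intense fluctuation is hypothesised to go with a more variable EQ-5D-5L index and with higher odds of counting past fluctuations in today's rating.

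**The concern.** Fluctuation means movement in both directions, and the Introduction describes dementia in those terms, as runs of good and bad days. A mean of signed changes removes exactly that pattern: each recovery offsets the deterioration before it. What is left is how far the patient ended from where they began, divided by the number of days.

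At stake is whether a primary outcome measures what it is named for. A reader of the results could see a mean intensity near zero and conclude that health is stable, in a sample with large daily swings. The same problem would reach the summaries of EQ-5D-5L change by intensity and the adherence regression if they used the signed mean. Patients would then be ordered from worsening to improving, not from stable to fluctuating.

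**Working it through.** The article gives no numerical result for intensity, so there is no figure to reproduce. The check scores example diaries on the article's own scale. The diary patterns are illustrative assumptions, not trial data.

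**Inputs.** Daily score d from −2 to +2 (Outcome measures section); 14 diary days (same section).

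**Formulas, for one patient with n = 14.**

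- Signed mean = Σd / 14
- Within-patient SD = √[Σ(d − mean)² / 13]
- Mean absolute change = Σ|d| / 14
- Frequency = number of days with d ≠ 0

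**Worked case, alternating +2 and −2.** Signed mean = (7 × 2 − 7 × 2) / 14 = 0.00. SD = √(14 × 4 / 13) = √4.308 = 2.08. Mean absolute change = 28 / 14 = 2.00. Frequency = 14.

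| 14-day diary | Signed mean | Within-patient SD | Mean absolute change | Frequency |
|---|---|---|---|---|
| Stable, all 0 | 0.00 | 0.00 | 0.00 | 0 |
| Alternating ±1 | 0.00 | 1.04 | 1.00 | 14 |
| Alternating ±2 | 0.00 | 2.08 | 2.00 | 14 |
| One bad day, then recovery (−2, +2) | 0.00 | 0.78 | 0.29 | 2 |
| Steady decline, −1 every day | −1.00 | 0.00 | 1.00 | 14 |

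1. The signed mean gives the first four diaries the same value. It singles out only the steady decline, which has no swings.
2. The within-patient SD separates the first four but gives the steady decline the same value as the stable patient.
3. The mean absolute change separates stable from every changing patient and orders the swings by size. It gives steady decline and alternating ±1 the same 1.00, so it needs the signed mean beside it to show direction.
4. Frequency does not cancel, but it gives alternating ±1 and alternating ±2 the same count of 14. It cannot stand in for intensity.

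**Random diaries.** Assume a change on a proportion p of days, independent between days, with +2, +1, −1 and −2 equally likely. The expected signed mean is 0 for any p. The expected mean absolute change is p × (1 + 2) / 2 = 1.5p.

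| p | Expected signed mean | Mean absolute change | Mean within-patient SD (simulated) |
|---|---|---|---|
| 0.10 | 0 | 0.15 | 0.41 |
| 0.50 | 0 | 0.75 | 1.10 |
| 0.90 | 0 | 1.35 | 1.49 |

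The zero in the second column follows from the assumed symmetry. The table shows how the measures behave; it does not predict the trial's data.

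**Classes.** If low, moderate and high were cut on the signed mean, low would hold the patients who worsened most, such as the steady decline at −1.00. Stable and alternating ±2 patients, both at 0.00, would share a class.

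**The case against.** The strongest reply has four parts.

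- **The SD is in the same sentence.** Taken within patient, it separates the alternating patient from the stable one. This stands, and the failure belongs to the mean alone. But the text does not say within patient, and an SD across patients is a group figure that cannot grade a dyad. Even within patient it misses steady drift.
- **The ± notation pairs worse with better at each level, and the class labels carry no direction.** Both are compatible with a magnitude reading, so signed averaging is the natural reading but not an explicit statement. The diary scale is plainly signed, however, and the summary is called a change. If magnitude is meant, one added word settles it.
- **Occurrence and frequency are reported separately and are also related to the outcomes.** This stands. A reader might infer that fluctuating patients look stable on every planned measure. They do not: the alternating patient has a frequency of 14 and the stable patient 0.
- **The derivation of the classes is not given, and a condensed article may leave it to the full protocol or analysis plan.** This stands. A reader might infer that the regression exposure carries no information on fluctuation and that its hypothesis is headed for a false null. The article never ties the classes to the signed mean, so that consequence is conditional.

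A reader might also infer that blank diary days count as no fluctuation, or that nearly everyone will have at least one fluctuation. The article says neither. At assumed daily rates of 5% and 10%, the chance of at least one in 14 independent days is 1 − 0.95¹⁴ = 51% and 1 − 0.90¹⁴ = 77%, which is not saturation. Counting episodes instead of daily changes, or replacing the three classes with a continuous exposure, would be a preference and not a correction.

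**Conclusion.** The point holds for the intensity summary. On the signed diary scale, and with no magnitude step written, the stated mean reflects net direction. It cannot distinguish a patient alternating ±2 from a stable one: 0.00 for both, against a mean absolute change of 2.00 and 0.00. The stated SD helps only under an unstated within-patient reading, and then not for drift.

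The conclusion rests on reading the summary on the scale as the diary defines it, which is the natural reading but not the only possible one. The example figures are arithmetic on assumed diaries. The effect on the adherence regression is conditional: it would test net drift if the classes were cut on the signed mean, and the article does not say whether they are. The study is exploratory and every daily score is recorded, so nothing is lost if the definition is settled before analysis.

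**What to change.** In Quantitative data preparation and analyses:

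1. Define intensity per dyad as the mean absolute daily change over completed diary days, Σ|d| divided by the number of completed days.
2. Report the signed mean separately, labelled as net direction, with the within-patient SD as a supplement.
3. State that the low, moderate and high classes are derived from the mean absolute change, in the adherence regression and wherever EQ-5D-5L change is presented by intensity.

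Occurrence and frequency can stay as they are. The cost is a few sentences of analysis wording. The diary, the visits and the sample size do not change.

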### Participant recruitment and eligibility criteria

PlwD and their informal caregiver will be recruited in the primary care setting through specifically qualified study nurses who work with general practitioners (GP), neurologists, psychiatrists and memory clinics who are in ongoing collaborations and studies with the German Center for Neurodegenerative Diseases (DZNE) at the site Rostock/Greifswald in Mecklenburg-Western Pomerania, a predominantly rural state in the north-eastern part of Germany. Study nurses will act as gatekeepers in this study as they may be perceived as trustworthy by participants due to their previous contact in other studies. Based on the means of recruitment, participants could have been included in other recently completed studies (ClinicalTrials.gov identifiers: NCT04741932, https://clinicaltrials.gov/ct2/show/NCT01401582, NCT03359408, NCT04037501; German Clinical Trials Register Reference No: DRKS00025074, DRKS00013555). After completing these studies, the study nurse checks the patient's and caregiver's eligibility criteria for this study, informs the dyad about the new study if they are eligible, and asks them to participate. If they were willing to participate again, they would be asked to provide written informed consent (IC) and be introduced to the study procedures. If this recruitment path does not yield sufficient participants, we plan to recruit from external settings, such as memory clinics. In some cases, informed consent might require a legal representative when informed consent cannot be acquired from the person with dementia due to severe cognitive impairment.

PlwD should meet the following inclusion criteria: positively screened for dementia through the DemTect procedure (DemTect ≤ 8) (12) or formally diagnosed with dementia by a treating GP, neurologist or psychiatrist. Eligibility criteria for caregivers are as follows: living in the same household or being in contact at least once a day (seeing the patient in person) with the PlwD.

Ethical approval has been obtained from the Local Ethical Committee at the University Medicine Greifswald (Registry number BB128/21 and BB 128/21a). The overall study design is illustrated in Figure 1.

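### The ICC by fluctuation-intensity group mixes between-patient spread with visit-to-visit variability, so a direct within-patient measure should be reported for the stated hypothesis

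*Protocol article*

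**What the plan says.** Under Quantitative data preparation and analyses, the protocol article names two statistics for EQ-5D-5L change by fluctuation intensity, the mean change and the ICC: "Also, change in EQ-5D-5L index, EQ-VAS and LLS will be demonstrated descriptively [mean value of change, Intra Class Correlation (ICC)] over the fluctuation intensity". The same section then hypothesises that frequent and more intensive fluctuation "will cause higher variability of the EQ-5D-5L index between baseline and seven or 14 days later".

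Two other statements bear on this:

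- Under Outcome measures to assess health fluctuations, the change scores for utilities, levels, level sum score and EQ-VAS "can be used to assess the variability and reliability of each measure". Two purposes are therefore named, variability and reliability.
- For the association between reported fluctuation and the differences between the three assessments, the article says "we will use appropriate statistics such as cross tables with ANOVA", with t-tests and logistic regression also listed. The logistic model has adherence to the recall period as its outcome, not EQ-5D-5L change.

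No within-patient SD, SD of change or absolute change is named for the EQ-5D-5L.

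**The concern.** The hypothesis asks whether a patient's index moves more from visit to visit when the diary shows more intense fluctuation. The ICC answers a different question, namely what share of the total variance lies between patients. Within one sample it is a recognised reliability index. Compared across groups, it moves with the spread of patients in each group as well as with visit-to-visit variation.

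The two components could well differ between intensity groups here. The groups are formed after enrolment from caregiver diaries, so nothing balances their case mix. Eligibility sets no limit on severity: a patient may be "positively screened for dementia through the DemTect procedure (DemTect ≤ 8") or have a formal diagnosis, and the recruitment section foresees severe impairment in some patients.

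At stake is how a descriptive table is read. A higher ICC in the high-intensity group could be taken as a more stable EQ-5D-5L there, when visit-to-visit variation is equal or larger.

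**Working it through.** **Inputs from the article.** Three EQ-5D-5L assessments per patient (baseline, day 7, day 14). Fifty dyads. Three intensity levels, "the fluctuation intensity (low, moderate, high"), which are given for the regression and without cut-points. The article states no ICC, SD or effect size, so there is no figure of its own to reproduce.

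**Assumptions.** All SDs below are illustrative values on the index scale. Equal groups give 50/3, or about 17 patients per group.

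**Formulas.** Let SDb be the between-patient SD and SDw the within-patient SD.

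- ICC = SDb² / (SDb² + SDw²)
- SD of change between two visits = √2 × SDw
- Dividing through by SDw² shows that the ICC depends only on SDb/SDw. The high group therefore has the larger ICC exactly when SDb(high)/SDb(low) exceeds SDw(high)/SDw(low). This is algebra and needs no assumed value.

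**Step 1: no true difference in within-patient variability.** SDw = 0.10 in both groups.

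- Low group, SDb 0.10: 0.0100 / (0.0100 + 0.0100) = 0.50
- High group, SDb 0.20: 0.0400 / (0.0400 + 0.0100) = 0.80

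The SD of change is √2 × 0.10 = 0.141 in both. The gap in the ICC comes entirely from case mix.

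**Step 2: the hypothesis is true.** SDw = 0.08 (low) and 0.12 (high), so SDw² is 0.0064 and 0.0144 and the within-patient ratio is 1.5. The SD of change is 0.113 versus 0.170 in every row. The last column is the simulated chance that the high group shows the larger ICC (17 patients per group, 3 visits, one-way ICC, 10,000 runs).

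| SDb low / high | Ratio of SDb | ICC low | ICC high | Reading | High group larger |
|---|---|---|---|---|---|
| 0.20 / 0.20 | 1.00 | 0.0400/0.0464 = 0.862 | 0.0400/0.0544 = 0.735 | right direction | 12% |
| 0.20 / 0.30 | 1.50 | 0.862 | 0.0900/0.1044 = 0.862 | no difference visible | 49% |
| 0.15 / 0.25 | 1.67 | 0.0225/0.0289 = 0.779 | 0.0625/0.0769 = 0.813 | reversed | 62% |
| 0.20 / 0.35 | 1.75 | 0.862 | 0.1225/0.1369 = 0.895 | reversed | not simulated |
| 0.10 / 0.25 | 2.50 | 0.0100/0.0164 = 0.610 | 0.813 | clearly reversed | 92% |

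In the four simulated rows, the within-patient SD ranked the two groups wrongly in only about 1% of runs, whatever the between-patient SD.

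**Step 3: do the other planned statistics cover it?** Mean change, ANOVA and t-tests all compare averages. The article does not say whether change is signed or absolute. If it is signed, a group in which half the patients gain 0.17 and half lose 0.17 has mean change (0.17 − 0.17)/2 = 0, the same as a group in which nobody moves. If absolute change were used, mean change would measure what the hypothesis asks.

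**The case against.** The strongest reply has four parts.

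1. The comparison is descriptive in a study that calls itself explorative, and no test of equal ICCs is planned. This stands. A reader might infer that the plan carries a high false-positive rate or low power. The documents do not support that: rejection rates would belong to a test that the plan does not contain.

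2. The ICC is not tied to the variability hypothesis. The article lists reliability among the purposes of the change scores, and the methods named for the association are ANOVA, t-tests and regression. This stands in part. A reader might infer that the authors will take a higher ICC as evidence against their hypothesis, but no passage says so. Still, the ICC is to be shown by intensity, next to a hypothesis about variability by intensity, and no named statistic measures within-patient dispersion directly.

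3. Reversal depends on chosen SDs. This stands. With equal spread the ICC points the right way, as the first row of the table shows, and with a wider spread in the low group it would point the right way even more strongly. A reader might infer that the ICC will mislead here, but the documents give no SDs from which to say how likely that is.

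4. The article condenses a fuller plan, and naming the ICC does not exclude reporting variance components. That is fair, and it is why the point is an improvement and not a fault of omission. The article does, however, state both the statistics and the stratifying variable, so the choice is open to comment.

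**Conclusion.** The point holds as a minor improvement, not as a demonstrated error. That an ICC compared across intensity groups is not a measure of within-patient variability is algebra: the ranking reverses whenever the between-patient SD ratio exceeds the within-patient SD ratio. Whether this happens in the trial is unknown. The sizes shown (0.50 versus 0.80 with identical visit-to-visit variability, and 0.610 versus 0.813 with the hypothesis true) rest on assumed SDs. The view that ANOVA and t-tests leave the gap open rests on change being signed, which the article neither states nor excludes. Use of the ICC as a reliability index for the whole sample is not in question.

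**What to change.** In Quantitative data preparation and analyses, amend the sentence on change in index, EQ-VAS and level sum score:

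- By intensity group, report the within-patient SD over the three visits (square root of the within-patient mean square) with a confidence interval. The SD of change or the mean absolute change would also serve.
- Keep the ICC as a reliability measure for the whole sample, or show the between- and within-patient variance components beside any group ICC.

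The components come from the same ANOVA or mixed model that yields the ICC. No new data are needed and nothing changes for participants. The cost is a wording change and one or two extra columns in a descriptive table.

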## Methods and analysis

### Study design and setting

To understand and explore the impact of health state fluctuations in dementia on the EQ-5D-5L assessment of today's health, this study will be carried out as an explorative, single-group, observational study that combines quantitative and qualitative (mixed) methods over the following four main study phases (see Table 1): (I) Quantitative baseline assessment (socio-demographics and clinical data) from both PlwD and family caregivers *via* interview at patients and caregivers home, (II) daily completion of the paper-pencil diary by the caregiver over 14 days, and (III) quantitative follow-up assessment *via* interview and (IV) qualitative semi-structured interviews at patients and caregivers homes after the 14 day assessment period.

**Table 1 T1:** Questions of the semi-structured interview.

**#**	**Question**
1	“Were you able to complete the diary every day?”.
2	“How easy or difficult was it for you to answer the diary? Why?”
3	“Were there any fluctuations in your relative's condition? What were the fluctuations?”
4	“Were the last 2 weeks typical of his/her normal situation?”
5	“What events did you note positively in the diary? What events did you note negatively in the diary? Why?”
6	“Are the events frequent? Can you describe how often they occur?”
7	“How exactly is your relative's condition affected? What areas of health were frequently affected?”
8	“Can you describe how important this area is to your relative's health?”
9	“Do you think your relative is aware of these fluctuations?”
10	“Now that we have discussed the diary entries, I want to talk about the 5-question questionnaire (EQ-5D-5L) you completed. Is the questionnaire a good reflection of the state of your health?”
11	“How easy or difficult was it for you to answer the questionnaire?”
12	“Are some questions more difficult than others? If so, why?”
13	“In the questionnaire, you are asked to describe your relative's CURRENT state of health. On all 3 days, did you only consider your relative's current state of health? Or did you include a longer time (yesterday or last week) when answering the questionnaire?”
14	“Thinking about the last 14 days, do you think your relative's health today is a good reference for their general health?”
15	“Do you have a suggestion for an alternative time of demand?”
16	“How often do you think this questionnaire (EQ-5D-5L) should be administered to better represent your relative's health?”

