### Sample size

The sample size in qualitative research is driven by data saturation. However, there are no standard criteria for calculating the sample size for this type of study. Blome et al. (9) set their sample size in the process guided by information power. We assume the sample size should be large enough to reveal at least *n* = 20 patients with health state fluctuations. Sun et al. (2) examined a sample size of *n* = 55 patients and found significant associations regarding fluctuations in HRQoL. However, the percentage of patients with dementia reporting health state fluctuations within 14 days is currently unknown. We, therefore, hypothesize that a sample size of *n* = 50 patient and caregiver dyads would be large enough to bear HRQoL outcomes (see health fluctuation outcomes below) and achieve the aims of this study.

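### The adherence model cuts a numeric diary intensity score into three levels although the hypothesis is a gradient; one numeric term would keep more power

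*Protocol article*

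**What the plan says.** All references are to the protocol article.

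- **Hypothesis** (Quantitative data preparation and analyses): frequent and more intensive fluctuations in the diary "will have higher odds for consideration of these fluctuations in the assessment of HRQoL today". The article equates this with not adhering to the recall period. The statement is a gradient: more intensity, higher odds.
- **Model** (same section): the regression "will include the adherence to the recall period (dichotomous: yes, no) as a dependent variable", and its independent variables are "the fluctuation intensity (low, moderate, high) and further socio-demographic and clinical variables of the patient as an independent variable". Whether the three levels are nominal or ordered is not stated.
- **Score** (same section, first paragraph): intensity is a daily diary value, "much worse or better = ±2; somewhat worse or better = ±1; about the same = ±0", summarised as an average daily change with its standard deviation. Nothing connects this quantity to the three levels.
- **Size and status**: the study is an "explorative, single-group, observational study". The Sample size section expects that "50 patient and caregiver dyads would be large enough to bear HRQoL outcomes" and says that "there are no standard criteria for calculating the sample size for this type of study". It gives no alpha, power or effect size.

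**The concern.** The diary yields up to 14 graded entries per patient, which average to a fairly fine numeric score. Reducing this to three levels treats all patients within a level as alike. If the levels are also entered as a class variable, the test has two degrees of freedom and looks for any difference between groups, including patterns such as a peak in the middle group that the hypothesis does not contain.

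The model addresses the last of the four primary outcomes and the third objective: whether past fluctuations are considered when health today is rated. With 50 dyads there is little power to spare, so avoidable loss in the one regression specified for this question matters.

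**Working it through.** **The plan's own figure.** There is none to reproduce, because no power or effect size is attached to the 50 dyads.

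**Inputs.** From the article: n=50, a yes/no outcome, a daily score of 0, ±1 or ±2 over 14 days, and three levels. Assumed: two-sided alpha 0.05; odds ratio per SD of intensity from 1.5 to 3.0; non-adherence of 30% or 50% at mean intensity; log-odds linear in the score; no covariates; three groups of about equal size.

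**Step 1: approximate formula.** For a 1-df test with 80% power the noncentrality is (1.960 + 0.842)² = 7.85.
- Spending a second degree of freedom on the same noncentrality gives 71% power.
- Grouping into thirds has an assumed relative efficiency of 0.793, so the noncentrality becomes 7.85 × 0.793 = 6.22.
- With 6.22, an ordered 1-df test has 70% power and an unordered 2-df test has 60%.

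From 80%, the loss is therefore about 10 points if the groups are scored in order and about 20 if they are a class variable.

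**Step 2: simulation.** Likelihood-ratio tests in logistic models, simulated 14-day diary score, n=50, 3,000 runs per row:

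| Non-adherence | OR per SD | Numeric term | Three levels, ordered | Three levels, class | Loss, ordered | Loss, class |
|---|---|---|---|---|---|---|
| 50% | 1.5 | 30.3% | 26.1% | 20.4% | 4.2 | 9.8 |
| 50% | 2.0 | 63.7% | 55.2% | 45.5% | 8.5 | 18.2 |
| 50% | 2.5 | 85.4% | 76.6% | 68.0% | 8.8 | 17.4 |
| 50% | 3.0 | 93.2% | 87.2% | 79.7% | 6.0 | 13.5 |
| 30% | 1.5 | 27.3% | 22.5% | 20.0% | 4.8 | 7.3 |
| 30% | 2.0 | 62.4% | 51.7% | 45.2% | 10.7 | 17.2 |
| 30% | 2.5 | 83.2% | 72.4% | 64.3% | 10.8 | 18.9 |
| 30% | 3.0 | 91.6% | 84.5% | 77.2% | 7.1 | 14.3 |

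With no association, the numeric and class tests rejected in 5.0-6.1% of runs, so the comparison is not driven by different error rates.

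**Step 3: sensitivity.**
- Including a normally distributed score, the class-variable loss at n=50 is 7-10 points at OR 1.5 and 13-20 points at OR 2 to 3.
- A second simulation with other diary assumptions gave 8-9 points at OR 1.5 and 11-18 points at OR 2 to 3 for a class variable, and 3-9 points for ordered levels.
- With three covariates added, the class-variable loss was about 10 points at OR 1.5 and 15-19 points at OR 2 to 3.

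**Step 4: which numeric score.** Take a patient with seven days at +2 and seven at −2. The signed mean is (7×2 − 7×2)/14 = 0, the same as for a patient who never changes. The mean absolute score is (7×2 + 7×2)/14 = 2, the maximum. When the gradient runs on the absolute score, a model with the signed mean had only about 6-9% power in simulation. A numeric term helps only if it ignores sign.

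**The case against.** Several points on the other side have force.

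1. **The coding is not stated.** A reader might infer from the reference to ANOVA, with no trend test named, that the three levels are unordered. The labels are naturally ordered and the article does not settle it. The larger losses are therefore conditional. Ordered coding still leaves a loss, because the grouping itself is stated.
2. **Other tests are allowed.** The section also names t-tests, in an open list. A t-test of numeric intensity by yes/no consideration had 73% power at OR 2.2 per SD, against 74% for the numeric logistic term, 66% for ordered levels and 56% for a class variable. The hypothesis thus need not rest on the three-level model alone. But the article does not say that this t-test will be done, and an unadjusted t-test does not replace the adjusted model it specifies.
3. **Cut points may be fixed elsewhere.** A reader might infer that, with no boundaries given, they will be chosen after seeing the data. In simulation, keeping the best of six pairs raises the false-positive rate to 16.6-20.1%, against 5.4-6.6% for one fixed pair. Nothing in the article says or implies such a search, and an analysis plan or full protocol that is not shown may fix the boundaries. This is no finding.
4. **The study is exploratory and the effect sizes are assumed.** Both are true. A linear truth also favours the numeric term, and at OR 1.5 power is low either way (25-31% against 17-21%). This limits the weight of the point but does not remove it, since the article states a directional hypothesis and a model for it.

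**Conclusion.** The point holds as a matter of efficiency: the article states a gradient hypothesis, defines a numeric daily score, and then specifies an adherence model that uses only three levels. At n=50, unadjusted, with a linear log-odds gradient and alpha 0.05, the cost against one numeric term is:

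- about 7-10 points of power at OR 1.5 per SD and about 11-20 points at OR 2 to 3, if the levels are a class variable;
- about 3-9 points, and up to 11 in one set of runs, if they are scored in order.

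A flat statement that the plan uses unordered groups and loses 15-25 points would go beyond the documents: the coding is not given, the effect size is not given, and the loss is under that range for weak gradients and for ordered levels. No stated calculation is wrong. The change is worth making because it is cheap and the sample is small.

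**What to change.** In Quantitative data preparation and analyses, replace the three-level intensity variable in the logistic model with one numeric term: the mean of the absolute daily diary scores (0, 1 or 2) over the 14 days. Report the odds ratio per unit or per SD with its confidence interval. State explicitly that the signed average is not the model term. Keep low/moderate/high for descriptive tables, derived from the same absolute score, so that one definition of intensity serves both uses.

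The cost is a sentence or two of analysis wording, with no extra data, visits or patients. The numeric term assumes a roughly linear log-odds gradient. Showing the proportion non-adherent in each of the three groups gives a simple check of that.
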